### Design of the atrioventricular delay haemodynamic optimization protocol

In this study, we use non‐invasive acute haemodynamic measurements to identify the optimal paced and sensed AV delays for individual patients.

In order to minimize the effect of noise, and so minimize the uncertainty of the optimization, we use the repeated alternation and parabolic fitting method. This approach has been shown to have a high level of reproducibility for determining the AV delay optimum. It has been described in detail previously and uses continuous non‐invasive beat‐by‐beat blood pressure using the Finapres Nova device (Finapres Medical Systems, The Netherlands).^32^ Briefly, continuous non‐invasive beat‐by‐beat blood pressure is recorded using the Finapres Nova device. Each tested AV delay is compared with a reference setting, and mean relative change in SBP is then calculated as the difference between the mean SBP at the reference setting (8 beats at the reference setting immediately before the transition) and the mean SBP at the tested setting (8 beats immediately after the transition to the tested AV delay). A minimum of six alternations are performed between the reference setting and atrial synchronous dual chamber His pacing and the mean of these alternations used to calculate the mean relative change for a particular programmed AV delay compared with the reference setting.

For sensed AV delay, the reference setting is sinus rhythm. For the atrial paced AV delay, the reference setting is AAI pacing at 10 b.p.m. above the patient's intrinsic rate.

The following programmed AV delays are tested: 40, 80, 120, 160, 200, 240, 280, and 320 ms, but the protocol is stopped if intrinsic ventricular activation occurs before 320 ms. *Figure*
*5* demonstrates the AV optimization process.

**Figure 5 ehf212315-fig-0005:**
[figure not shown]
Atrioventricular (AV) delay optimization protocol. The relative change in systolic blood pressure (SBP) between 8 beats of AAI pacing and 8 beats of dual chamber atrial synchronous–His pacing at a given atrioventricular delay (AVD) is determined [AV delay = 80 ms in this example (top left)]. This is a single alternation (plotted bottom left). A minimum of six alternations are made for each AVD (middle sections top and bottom). This process is repeated for each AV delay between 40 and 320 ms (less if intrinsic AV conduction occurs before 320 ms). The optimal AV delay is then derived from the plotted parabola (bottom right). In this example, the optimal AV delay was 160 ms. BP, blood pressure; ECG, electrocardiogram.

#### Analysis plan

All study data are being recorded in our institution's clinical trial database (Inform, version 4.6). The trial is conducted through the Imperial College Clinical Trials Unit, which provides monitoring and trial oversight to minimize the amount of missing data.

The primary endpoint is peak oxygen uptake measured using cardiopulmonary exercise testing. The primary outcome will be analysed using a two‐level hierarchal model. We will include treatment, period, and sequence effect within the model. Random subject effects will also be included in the regression model if appropriate. Differences in secondary outcomes will also be analysed using a two‐level hierarchal model. Normality will be checked, and appropriate transformation or non‐parametric methods will be used if it is not met.

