## Methods

### Trial purpose

The HOPE‐HF trial is designed to evaluate the effects of AV optimized His‐bundle pacing for patients with left ventricular systolic dysfunction and PR prolongation but without LBBB. The primary endpoint is the within‐patient difference in exercise capacity with His optimized pacing compared with no pacing in a crossover trial with 6 month treatment periods. Secondary endpoints are quality of life (QOL), echocardiographic measurements, B‐type natriuretic protein (BNP) measurements, and daily patient activity levels.

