#### Follow‐up duration

The study endpoint measurements are conducted at three set time points. Baseline measures are taken 2 months after the device has been implanted (during which time no His pacing is performed). The duration of each treatment arm is 6 months, to allow time for cardiac remodelling and to minimize any carryover effect. Further endpoint assessments take place 6 months after the baseline visit while patients have had either His pacing programmed on or off and then after a final 6 month interval following crossover to the alternate arm. Assessment of adverse events is continuous throughout the trial.

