**Figure 4 ehf212315-fig-0004:**
[figure not shown]
Patient study flow chart (AV, atrioventricular; BNP, B‐type natriuretic protein; ICD, implantable cardioverter defibrillator; QOL, quality of life).

Two months after implantation, study participants visit the core centre to have baseline measurements recorded, which includes all endpoint measurements. AV delay optimization is performed using continuous non‐invasive blood pressure. Patients are then randomized to 6 months of AV optimized His pacing or 6 months of no His pacing. At the end of each 6 month period, all the endpoints are measured. Patients then enter the other arm of the study.

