### Sample size calculation

The smoothed modified Bruce protocol in patients with heart failure has a test–retest variability of 2.4 mL/kg/min.^29^ Implantation of a CRT‐P in patients with broad QRS duration and heart failure results in a 0.5–2.5 (mean 1.5) mL/kg/min increase in peak oxygen uptake.^34^, ^35^ Acute haemodynamic data suggest that the benefit from His‐bundle pacing in long PR narrow QRS patients is around 60% of the effect seen with CRT in LBBB patients.^24^ We might therefore expect that the estimated increment in peak oxygen uptake of 60% would be 0.9 mL/kg/min. One hundred and twenty six patients would give 90% power at the 5% significance level to detect a 0.7 mL/kg/min change. To account for combined mortality and dropout rates as high as 21%, we will recruit 160 patients.

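### Baseline peak VO2 is measured before randomisation but not named in the stated primary model; naming it, with an unconditional patient effect, is a free but small gain confined to patients who give period 1 only

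*Protocol article*

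**What the plan says.** The Analysis plan section describes a two-level hierarchical model for the primary outcome and lists its terms: "We will include treatment, period, and sequence effect within the model". It adds: "Random subject effects will also be included in the regression model if appropriate". Baseline peak VO2 is neither named nor ruled out. The secondary outcomes get the same type of model.

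The baseline value exists. Follow-up duration states: "Baseline measures are taken 2 months after the device has been implanted". The text under Patient flow, after the Figure 4 caption, says that "study participants visit the core centre to have baseline measurements recorded, which includes all endpoint measurements", and later in the same paragraph: "Patients are then randomized to 6 months of AV optimized His pacing or 6 months of no His pacing". So peak VO2 is measured before allocation in every patient.

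Trial purpose defines the primary contrast within the patient, as the "difference in exercise capacity with His optimized pacing compared with no pacing in a crossover trial with 6 month treatment periods". The Sample size calculation plans on 126 patients and recruits 160 to allow for "combined mortality and dropout rates as high as 21" per cent. The Compliance and loss to follow-up section commits to intention to treat.

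**The concern.** Some patients will probably be tested at the end of period 1 and then die or withdraw before the second test. For them the treatment comparison is between patients. Without baseline it carries the full between-patient variance and is largely confounded with the sequence term, because in period 1 sequence and treatment coincide. A pre-randomisation value of the same measurement would remove much of that variance.

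The second strand is missing data. A likelihood analysis of incomplete crossover data assumes that loss is random given what the model contains. The Primary endpoint section itself calls peak VO2 a strong predictor of mortality in heart failure, so loss may well depend on baseline capacity.

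At stake are some precision and some robustness in the part of the estimate that comes from one-period patients. No figure in the plan is at stake.

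**Working it through.** **1. Inputs.** From the Sample size calculation: "variability of 2.4 mL/kg/min", difference 0.7 mL/kg/min, 5% significance, 90% power, 126 evaluable patients, 21% loss, 160 recruited. From Randomization and allocation concealment: 1:1 allocation. Assumed, because the article does not give them:
- between-patient SD σ_b of 3, 4 or 5 mL/kg/min;
- number m with period 1 only: 0, 8, 17 or 34, where 34 = 160 − 126 means that every lost patient is lost after the first follow-up test;
- equal correlation between baseline, period 1 and period 2.

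**2. The plan's own figure.** With 2.4 as the SD of the within-patient difference and a two-sided test:
- n = (2.4 × (1.960 + 1.282) / 0.7)² = 123.5, so 124 by the normal approximation;
- power at n = 126 by the noncentral t distribution is 90.1%;
- 126 / 0.79 = 159.5, so 160.

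The figures reproduce without any use of baseline.

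**3. Patients with both periods.** Let B be baseline and Y1, Y2 the two period values. Then Cov(Y1 − Y2, B) = σ_b² − σ_b² = 0, so B carries no information on the within-patient difference. The treatment variance from 126 completers is 2.4² / 126 = 0.04571 (SE 0.2138) with or without baseline. Power by Φ(0.7/SE − 1.96) is 90.6%.

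**4. Patients with period 1 only.** The within-patient variance is σ_w² = 2.4² / 2 = 2.88 (SD 1.70). The variance of Y1 is σ_b² + σ_w². Given baseline it falls to (σ_b² + σ_w²) − σ_b⁴ / (σ_b² + σ_w²):
- σ_b = 3: 11.88 falls to 11.88 − 81 / 11.88 = 5.06;
- σ_b = 5: 27.88 falls to 27.88 − 625 / 27.88 = 5.46.

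The reduction per patient is large, but few patients are affected and the sequence term still absorbs part of their contrast.

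**5. Whole trial.** The generalised least squares variance of the treatment effect is the treatment element of (Σ Xᵢ′ Vᵢ⁻¹ Xᵢ)⁻¹, with Vᵢ = σ_b² J + σ_w² I. Here J is the all-ones matrix and I the identity. Fixed effects are treatment, period and sequence, and there are 126 completers plus m one-period patients. Baseline enters as a repeated measure with one mean common to both sequences.

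| m | σ_b | Variance without baseline | Variance with baseline | Information gain | Power (normal approx.) |
|---|---|---|---|---|---|
| 0 | 3–5 | 0.04571 | 0.04571 | 0 | 90.6% → 90.6% |
| 8 | 3 | 0.04538 | 0.04494 | 1.0% | 90.8% → 91.0% |
| 8 | 5 | 0.04557 | 0.04499 | 1.3% | 90.6% → 91.0% |
| 17 | 3 | 0.04506 | 0.04417 | 2.0% | 90.9% → 91.5% |
| 17 | 5 | 0.04543 | 0.04428 | 2.6% | 90.7% → 91.4% |
| 34 | 3 | 0.04454 | 0.04295 | 3.7% | 91.3% → 92.2% |
| 34 | 4 | 0.04497 | 0.04309 | 4.4% | 91.0% → 92.1% |
| 34 | 5 | 0.04521 | 0.04315 | 4.8% | 90.9% → 92.1% |

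Information gain is the ratio of the two variances minus 1. In power points, from unrounded values, the gain is 0.3 to 0.35 for m = 8, 0.5 to 0.7 for m = 17, and 0.9 to 1.2 for m = 34. The largest fall in SE is from 0.2126 to 0.2077, about 2.3%.

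**6. What one-period patients add.** Relative to completers alone, 34 such patients add 0.04571 / 0.04454 − 1 = 2.6% information at σ_b = 3 and 0.04571 / 0.04521 − 1 = 1.1% at σ_b = 5, using a random patient effect and no baseline. With baseline they add 6.4% and 5.9%.

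**The case against.** The strongest reply is that this is an efficiency preference about a covariate list, which a condensed article commonly leaves to the SAP. The listed terms are standard for a two-period crossover, and the text does not say that they are the only ones. This stands to the extent that silence does not prove exclusion and nothing in the article is wrong. But the article does state a model and makes the patient effect conditional, so a suggestion on that model is legitimate.

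Three stronger readings are tempting and are not supported:
- *That up to 21% will give only one period.* The 21% is a ceiling on death and dropout combined. It includes patients lost before the first follow-up test, who have no outcome for baseline to help. The article does not say how the losses divide.
- *That one-period patients are wasted under the stated model.* With a random patient effect they already contribute, though only 1.1% to 2.6% even when there are 34 of them. Under fixed patient effects they would contribute nothing, and a baseline covariate would not change that. The conditional wording therefore matters at least as much as the missing baseline term.
- *That leaving out baseline biases the result.* Loss that depends only on a patient's overall capacity does not bias a within-patient contrast. If severity changes the treatment effect, a baseline main effect would not cure it. A one-period patient's own period 1 value, itself a marker of severity, is already in the likelihood. Baseline strengthens missing at random only for the small between-patient component.

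It is also fair to say that the size of the gain rests on assumed values. A weaker correlation between baseline and period 1 would shrink it.

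**Conclusion.** The point holds as a minor improvement. Baseline peak VO2 is collected before randomisation and not named in the stated primary model, and the patient effect is conditional. Adding baseline yields nothing for completers and leaves the 126/160 sample size and the 90% power as they are. With 8 to 34 period-1-only patients it yields about 1% to 4.8% more information, roughly 0.3 to 1.2 power points. The upper end needs the full 21% loss with every loss after the first follow-up test.

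These figures rest on an assumed between-patient SD of 3 to 5 mL/kg/min, a within-patient SD of 1.70 derived from the test–retest figure and carried across 6-month intervals, equal correlation between visits, and the sequence term kept. The gain in robustness is real in principle but limited, and no bias has been demonstrated.

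**What to change.** In the primary model:
- include the random patient effect unconditionally;
- enter baseline peak VO2 as a pre-randomisation repeated measure with a mean common to both sequences, with the sequence term applying only to post-randomisation values, or alternatively as a covariate;
- include every randomised patient with at least one post-baseline value.

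Do the same for each secondary outcome that has a baseline value. If the SAP already specifies this, it is enough to confirm it.

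The cost is a line or two in the analysis plan. The data are already collected, and neither the sample size nor the visit schedule changes.

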### Planned subgroup analysis

#### Right bundle branch block cohort

We expect one‐third of recruited patients to have RBBB. In these patients, His‐bundle pacing may shorten QRS duration by overcoming the RBBB (Supporting Information, *Figure*
*S1*). Therefore, patients may theoretically obtain benefit from ventricular resynchronization in addition to that obtained from optimization of AV delay. Narrowing of QRS may occur by (i) positioning the pacing lead distal to the site of bundle branch block leading to an electrical bypass of the block; (ii) overcoming the block with sufficient stimulus to activate distal dormant tissue, relying on either source–sink relationships during pacing vs. intrinsic impulse propagation or the virtual electrode polarization effects or (iii) retrograde activation via capture of an upper septal branch of the His‐Purkinje system or (iv) in the case of non‐selective His‐bundle capture partial or full correction of the terminal RBBB pattern by fusion without recruiting the RBB fascicles.

We will perform a subgroup analysis to test for the possibility that RBBB patients show a larger benefit than the narrow QRS patients, which might signify the presence of dual benefit in bundle branch block patients.

#### PR interval

We will test whether there is a relationship between magnitude of improvement in the outcome measures with AV optimized His pacing and baseline PR interval. Such a relationship might be expected if there is a benefit from PR interval shortening. The PR interval of 200 ms or above was chosen as the entry for the HOPE‐HF because in the COMPANION trial, patients with a PR interval longer than 200 ms appeared to obtain greater benefit from CRT.^33^ However, the MADIT‐CRT study reported a larger difference in those whose PR interval was >230 ms^2^; we wanted to recruit a broad range of patients who might permit later evaluation of the effect of PR interval.

#### E‐A wave analysis

We will test whether the presence of E‐A wave fusion predicts the size of any His pacing benefit.

Baseline E‐A wave fusion on echocardiography suggests that there is inefficient left ventricular filling, and it is possible that it may be useful in selecting patients who are likely to benefit from AV optimization with His pacing.

#### Selective vs. non‐selective His capture

If there are significant numbers of patients with non‐selective His capture, we will perform an analysis to assess whether the type of His capture affects the outcome measures.

### Sample size calculation

The smoothed modified Bruce protocol in patients with heart failure has a test–retest variability of 2.4 mL/kg/min.^29^ Implantation of a CRT‐P in patients with broad QRS duration and heart failure results in a 0.5–2.5 (mean 1.5) mL/kg/min increase in peak oxygen uptake.^34^, ^35^ Acute haemodynamic data suggest that the benefit from His‐bundle pacing in long PR narrow QRS patients is around 60% of the effect seen with CRT in LBBB patients.^24^ We might therefore expect that the estimated increment in peak oxygen uptake of 60% would be 0.9 mL/kg/min. One hundred and twenty six patients would give 90% power at the 5% significance level to detect a 0.7 mL/kg/min change. To account for combined mortality and dropout rates as high as 21%, we will recruit 160 patients.

### Compliance and loss to follow‐up

It is anticipated that some patients may request a change in their treatment arm, particularly if there is a change in their symptom status. If this occurs, we will try to encourage patients to continue with their designated treatment until they cross over or complete the study as scheduled. If however the clinical team judges that it is necessary to turn on or off His pacing, this will be performed. Analysis will be on the standard intention to treat basis.

Follow‐up will be coordinated and carried out by a research team dedicated to this study. If patients decide they no longer wish to attend the core centre for follow‐up, then we will ask if they are willing at least to be contacted by the research team to ensure data on adverse events can be recorded.

### Steering committee

This committee is responsible for developing and monitoring the implementation of the protocol. The committee is supported by a statistician independent of the sponsor and is responsible for ensuring timely publication of the results.

### Data Safety Monitoring Board

The Data Safety Monitory Board (DSMB) is responsible for monitoring patient safety and will recommend that the trial is stopped prematurely if a significant increase in all‐cause mortality is noted in the active His pacing arm. The DSMB may request interim analyses should the safety data indicate that treatment is associated with important adverse events.

### Adverse events

All adverse events will be documented and reviewed by the study‐specific DSMB. Serious adverse events are defined as those which are not anticipated or not known to be related to the condition being studied or the intervention being used that would result in any of the following outcomes: death, life‐threatening condition, unexpected/unplanned inpatient hospitalization, and persistent or significant disability or incapacity.

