**Methods and results:**

This multicentre, double‐blind, randomized, crossover study aims to randomize 160 patients with PR prolongation (≥200 ms), LV impairment (EF ≤ 40%), and either narrow QRS (≤140 ms) or right bundle branch block. All patients receive a cardiac device with leads positioned in the right atrium and the His bundle. Eligible patients also receive a defibrillator lead. Those not eligible for implantable cardioverter defibrillator have a backup pacing lead positioned in an LV branch of the coronary sinus. Patients are allocated in random order to 6 months of (i) haemodynamically optimized dual chamber His‐bundle pacing and (ii) backup pacing only, using the non‐His ventricular lead.

The primary endpoint is change in exercise capacity assessed by peak oxygen uptake. Secondary endpoints include change in ejection fraction, quality of life scores, B‐type natriuretic peptide, daily patient activity levels, and safety and feasibility assessments of His‐bundle pacing.

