#### Secondary endpoints

Secondary endpoints include echo measurements of LV volume, plasma concentration of BNP, QOL scores, daily patient activity levels, and hospitalization episodes.

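### The serious adverse event definition mixes outcome with expectedness and relatedness, so counts of serious events would be too low

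*Protocol article*

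**What the plan says.** The definition is a single sentence in the Adverse events section. It opens: "Serious adverse events are defined as those which are not anticipated or not known to be related to the condition being studied". It continues: "or the intervention being used that would result in any of the following outcomes: death". The remaining outcomes are a life-threatening condition, unplanned inpatient admission, and lasting or significant disability or incapacity.

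Four other statements bear on it:

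- The sentence just before the definition begins: "All adverse events will be documented and reviewed by the study", and names the trial's own DSMB as the reviewer.
- The Data Safety Monitoring Board section says that the board "will recommend that the trial is stopped prematurely if a significant increase in all"-cause mortality is seen in the active arm. It adds: "The DSMB may request interim analyses should the safety data indicate that treatment is associated with important adverse events".
- The Secondary endpoints section ends its list with "daily patient activity levels, and hospitalization episodes".
- The abstract (Methods and results) includes "safety and feasibility assessments" of His-bundle pacing among the secondary endpoints.

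**The concern.** Three attributes of an adverse event are normally kept apart: how bad the outcome was (seriousness), whether it was foreseen (expectedness), and whether it is attributed to the disease or the intervention (relatedness). The sentence makes the first depend on the other two. As worded, a death can be classed as not serious because it was an anticipated death from heart failure. A recognised lead complication that leads to an unplanned readmission can be classed as not serious because it is a known effect of the device.

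This matters because His-bundle pacing is attempted in every patient and its safety is named as a secondary endpoint. Recognised device complications with serious outcomes are central to that endpoint. A reader of the results will take a serious-event count to be complete by outcome. Under this definition it would not be. With about 20 sites, a clause that can be read in two ways may also be applied differently from site to site.

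**Working it through.** No arithmetic applies, because the point depends on no rate, power or sample size. The check sets the wording out logically and then compares it with the other safety provisions.

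**Step 1: the wording.** Take an event that has one of the listed outcomes. Let A mean that it was anticipated. Let R mean that it is known to be related to the condition or to the intervention, reading the negation as covering both.

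- Outcome alone: every such event is serious.
- Literal or: serious if (not A) or (not R), so excluded only if A and R both hold.
- Stricter reading: serious only if (not A) and (not R), so excluded if either holds.

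| A | R | Illustration (mine) | Outcome alone | Literal or | Stricter reading |
|---|---|---|---|---|---|
| no | no | unforeseen admission with an unrelated cause | serious | serious | serious |
| no | yes | unforeseen kind of device complication | serious | serious | excluded |
| yes | no | foreseen admission for another illness | serious | serious | excluded |
| yes | yes | expected heart failure death or admission; recognised lead complication needing readmission | serious | excluded | excluded |

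The last row is excluded on both readings, so settling the meaning of or would not repair the definition. It would decide only the two middle rows.

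**Step 2: is the last row likely to be empty?** The document itself foresees events of this kind. The device implantation text provides a backup lead partly in case the His lead stops working, and the sample size section allows for deaths. Such events are therefore anticipated, and those due to heart failure or the lead are also related.

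**Step 3: where those events still appear.**

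- Documentation and DSMB review cover all adverse events, whatever their label.
- The mortality rule covers all causes, so a heart failure death counts.
- The DSMB's trigger for interim analyses refers to important adverse events, not to events labelled serious.
- Hospitalization episodes are a secondary endpoint with no exclusion by cause.
- The Follow-up duration section makes adverse event assessment continuous.

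**Step 4: what remains affected.** Only outputs that use the serious label: the serious-event count, and any reporting or summary restricted to serious events. The document does not say that the safety endpoint is limited to such events.

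**The case against.** The strongest reply is that nothing is lost. The DSMB sees every adverse event, the mortality rule is all-cause, and admissions are counted separately. The definition does not touch randomization, the primary endpoint, its analysis or the sample size. The article also condenses a full protocol that may word the definition differently.

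Most of this stands, and it limits the point. A reader might infer that the safety results would leave these events out, or that the DSMB would see a falsely low event rate. The documents do not support either inference: review does not depend on the label, and nothing confines the safety results to serious events. A reader might also say that every known device complication is excluded. On the literal or, an unanticipated one still qualifies.

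The other routes do not fully replace a correct label, however. The mortality rule concerns the active arm, while randomization comes two months after implantation, so it does not address procedural or early lead harm. Hospitalization counts do not by themselves identify device-related serious harm. Apart from the adverse event records, no listed endpoint covers a life-threatening or disabling event that is neither fatal nor leads to admission. As for condensation, the article states the definition rather than leaving it to the full protocol, so the sentence can be judged as it stands.

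**Conclusion.** The definition is wrong as written. On either reading, events that are both anticipated and known to be related to heart failure or the device are not classed as serious, whatever their outcome. The effect is misclassification: serious-event counts, and any reporting that depends on that label, would be understated for the safety endpoint named in the abstract. Capture of the events, DSMB review and mortality monitoring are unaffected.

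The direction is certain once any such event occurs, because outcome alone can only add events. The size cannot be derived, since the article gives no rates of heart failure deaths, admissions or lead complications. The 21% in the sample size section cannot stand in for one: it is a planning allowance that combines deaths with dropout.

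The conclusion assumes that the sentence is applied as published, and that some safety output uses the serious label.

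**What to change.** - Define a serious adverse event by outcome alone (death, life-threatening condition, unplanned hospitalization, persistent or significant disability or incapacity), whatever its cause or expectedness. The hospitalization item currently pairs unplanned with unexpected; keep only unplanned, so that expectedness does not return through the outcome list.
- Record relatedness (separately for procedure, lead and pacing) and expectedness as their own fields.
- Relabel the adverse events already logged since recruitment began in January 2016. Since all adverse events are documented, this should need no new patient contact.

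The cost is one protocol sentence, the added case report form fields and a one-off relabelling. The reported number of serious events will rise, and the report should say that this reflects the corrected definition. Treatment, design and the primary analysis do not change.
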